## Abstract

**Background:**

Patients are at risk of drug-related problems (DRPs) at transition points during hospitalization. The community pharmacist (CP) is often the first healthcare professional patients visit after discharge. CPs lack sufficient information about the patient and so they may be unable to identify problems in medications, which may lead to dispensing the wrong drugs or dosage, and/or giving wrong information. We aim to assess the impact of a complex intervention comprising of medication reconciliation performed at discharge by a hospital pharmacist (HP) with communication between the HP and CP on DRPs during the seven days following discharge.

**Methods/Design:**

The study is a cluster randomized crossover trial involving 46 care units (each unit corresponding to a cluster) in 22 French hospitals during two consecutive 14-day periods, randomly assigned as ‘experimental’ or ‘control’ (usual care) periods. We will recruit patients older than 18 years of age and visiting the same CP for at least three months. We will exclude patients with a hospital length of stay of more than 21 days, who do not return home or those in palliative care. During the experimental period, the HP will perform a medications reconciliation that will be communicated to the patient. The HP will inform the patient’s CP about the patient’s drug therapy (modification in home medication, acute drugs prescribed, nonprescription treatments, and/or lab results). The primary outcome will be a composite outcome of any kind of drug misuse during the seven days following discharge assessed at day seven (±2) post-discharge by a pharmacist in charge of the study who will contact both patients and CPs by phone. The secondary outcome will be unplanned hospitalizations assessed by phone contact at day 35 (±5) after discharge. We plan to recruit 1,176 patients.

**Discussion:**

This study will assess the impact of a reconciliation of medications performed at patient discharge followed by communication between the HP and the patient’s CP. It will allow for identifying the type of patients in France for which the intervention is most relevant.

**Trial registration:**

This study was registered with ClinicalTrials.gov (number: NCT02006797) on 5 December 2013.

## Background

Drug-related problems (DRPs) are defined as an ‘event or circumstance involving drug therapy that actually or potentially interferes with desired health outcomes’
[1]. These problems are the cause of about 11% of the iatrogenic problems and could be avoided.

In France, the national survey of all serious adverse events associated with care (ENEIS) showed that 1.3% of hospitalizations (between 100,000 and 120,000 a year) are due to a serious drug-related iatrogenic event and are therefore avoidable
[2]. Furthermore, more than half occur after a new prescription at admission or during discharge. In fact, the French health authority, through an accreditation procedure, requires hospitals to ensure treatment continuity from admission to discharge
[3].

An estimated 7 to 30% of patients present a DRP at hospital admission
[4]. A reconciliation of medications supported by efficient communication between the hospital staff and community pharmacists (CPs), in addition to a standard patient interview and a general practitioner’s examination of prescriptions, was found to be effective in identifying medication discrepancies for inpatients
[5,6]. Approximately 25 to 87% of patients experience DRPs after hospital discharge
[7-14]. Drug reconciliation before discharge was also found to be effective and could decrease DRPs by 50% when performed by a medical and/or pharmaceutical team; pharmaceutical teams were more effective in this process than medical or nursing teams
[15-18].

Medication reconciliation is defined as the formal process of checking the complete, accurate list of a patient’s previous medication and comparing it with the prescriptions after a transition of care (on admission, after transfer to another medical unit, and at discharge)
[19]. The process has been recommended since 2005 by the Joint Commission on Accreditation to prevent errors. Countries such as Germany, the Netherlands, and France are involved in the World Health Organization (WHO) High 5’s procedure and particularly in medication reconciliation at admission
[20,21]. Discrepancies between hospital treatment and home medication must be discussed with the prescriber and modifications made if necessary
[19]. In fact, non-intentional discrepancies (NIDs) or intentional discrepancies (IDs) may be observed. An ID is a voluntary change in the patient’s medication (unnecessary drugs, route or dose change, or conformation to the hospital formulary). NIDs (wrong route or dose, missing treatment, or added drug) are considered medication errors. Among NIDs, 40 to 59% are potential causes of adverse events and 33% actually lead to adverse events
[19].

Several experiments have been conducted in North America or Europe to increase the quality of information at discharge, considering that well-informed patients and/or caregivers can manage the drug treatment on their own. However, few studies have focused on the role of the CP at discharge, both in the reconciliation process and/or the information needed to reduce DRPs (such as the medical discharge letter)
[22,23].

The primary objective of this study is to investigate a hospital pharmacist (HP) performing a reconciliation of medications with the patient at discharge, followed by communication between the HP and the CP, and their impact on the incidence of DRPs in patients during the seven days after discharge. The potential harmfulness of DRPs will be appraised by an expert committee. Secondary objectives are patient satisfaction and subgroup analyses.

## Methods/Design

### Design

This study will be a cluster randomized crossover controlled trial. The clusters will be hospital units, each involved during two consecutive 14-day periods (one when the assessed intervention will apply and the other as the control period). For each unit, the order of the two periods will be randomized (intervention followed by control, or vice versa).

We planned the study as a cluster trial because of methodological issues. Indeed, randomization of patients would have implied fully informing them of the study, thus increasing the risk of group contamination. Conversely, randomizing clusters allows for patients to receive partial information; patients included in the usual care group will be unaware that some patients will have a reconciliation procedure performed at discharge. Therefore, we planned the study as a crossover trial because: 1) the risk of cross-contamination is minimal (residual effect on a short period is null); 2) even if a residual effect exists, it is a superiority test that would lead to minimizing the intervention effect; 3) the crossover trial allows for increasing the statistical power and thereby balancing the power lost with the cluster design
[24]; and 4) a crossover design offers better balance between groups, which is of importance in our study due to the high heterogeneity in units.

### Setting and participants

In total, 22 French HPs working in hospitals all over the French country have agreed to participate. Each HP selected two units (one surgical, one medical) in their hospital. Units for which a pharmaceutical reconciliation procedure at admission or discharge was already in place were not eligible. The medical heads of the units also agreed to participate. We will exclude patients with a length of stay of more than 21 days (as there can be too many therapeutic modifications during the stay), who do not return home, who are in palliative care and/or near the end of life, and who are not able to understand the topic.

CPs working in the area around the hospital will participate by the inclusion of their patients in the study. They will be informed of the study in three ways: a professional journal supported by the pharmacist unions, a professional journal supported by the national council of the order of pharmacists, and a letter sent by the study scientific committee distributed by wholesale drug distributors.

### Outcomes

The primary outcome is a composite one comprising of any problem or dysfunction observed during the seven days after discharge. More specifically, we will consider any of the following problems: 1) the drug is not the correct one (name, form, route, or dose); 2) the patient does not take what was prescribed and/or takes treatments that should have been stopped; and 3) the patient could not obtain the medication when visiting the pharmacy, which causes a gap in the continuity and duration of therapy.

The primary outcome will be assessed at day seven (±2) after discharge, by a pharmacist specifically recruited for the study. This pharmacist will contact both patients and CPs by phone to assess the possible incidence of a DRP after discharge.

For each DRP, an expert committee composed of physicians (one nephrologist, one cardiologist, one gastroenterologist, and a clinical pharmacist) will assess the potential medical impact of the DRP in terms of its severity (from 0: no problem, to 3: life-threatening) using Bayliff’s scale
[25]. The severity of the identified DRP will be one of the secondary outcomes.

Other secondary outcomes will be: 1) the number of non-planned hospitalizations during the 35 days after discharge (assessed by phone by the pharmacist recruited for the study); and 2) patients and CP satisfaction (assessed at day seven with a four-item Likert scale by phone). We will also assess the time taken by the HP to perform the intervention (medication reconciliation and communication to CP) and the proportion of drug prescriptions modified by the HP at discharge. DRP will be studied in following five subgroups: 1/less or over or equal to 75-years-old, 2/less or over or equal to 4 drugs prescribed 3/expensive or not-expensive medication 4/surgery or medical-unit and 5/planned or non-planned hospitalization.

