### Sample size calculation

This study is a superiority trial with a binary decision criterion. We hypothesized a DRP rate of 45% in the experimental group as compared to 60% in the control group
[7]. Considering a 90% power and a 5% two-sided alpha level, we would need 235 patients per group with a trial of two parallel, individually randomized groups. We used a sample size calculation software (nQuery Advisor -2005- Version 6.0 Los Angeles, CA. Copyright © 2005 by Janet D. Elashoff). In addition, because the trial is a cluster randomized crossover trial, we assessed both intraclass and interclass correlations
[24,28]. We therefore applied an inflation factor equal to:

(1)$$1\;+\;\left(P\;–1\right)\rho -\mathrm{P\eta}$$

where *P* is the number of patients in a cluster, *ρ* is the intraclass correlation coefficient and *η* is the interclass correlation coefficient. We considered a high value for the intraclass correlation coefficient because the outcome is a process, and because of the incidence of about 50%
[29]. Naturally, *η* is expected to be lower than *ρ*, and we chose the value of *η* to be half that of *ρ* as advised
[24]. We will use a value of 0.2 for *ρ* and 0.1 for *η*.

Because we identified 46 units, we planned to recruit 10.2 patients in each unit for each period. We plan to perform a sensitivity analysis excluding patients without data at day seven after discharge, and so we fixed the number of patients to be recruited in each period to 14. In the end, we expect to recruit 14 patients in each of the 46 units in each period, for 1,176 patients.

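### The seven-day DRP outcome and the 35-day hospitalization outcome may be assessed before their periods end, which modestly understates the rates and attenuates the effect

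*Protocol article*

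**What the plan says.** The Outcomes section of the protocol article defines the primary outcome as "any problem or dysfunction observed during the seven days after discharge" and then states "The primary outcome will be assessed at day seven (±2) after discharge". The abstract (Methods/Design) joins the two in one sentence: "any kind of drug misuse during the seven days following discharge assessed at day seven (±2) post-discharge". The call may therefore fall anywhere from day 5 to day 9.

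The hospitalization outcome follows the same pattern. Outcomes counts "the number of non-planned hospitalizations during the 35 days after discharge", and the abstract describes "unplanned hospitalizations assessed by phone contact at day 35 (±5) after discharge", which is days 30 to 40. The ±5 appears only in the abstract.

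The article states one call per outcome. It mentions no repeat call for a patient reached before the period has ended. The Sample size calculation section plans a sensitivity analysis without patients who lack day-seven data. On its ordinary reading this does not cover a patient who was reached on day 5, because that patient has data. The Blinding section says the study is open and that the outcome assessor is not blinded.

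**The concern.** The lower half of each window lies inside the period that the call is meant to cover. A patient called on day 5 with no problem so far has two days still to come, and nothing in the article says those days are ever observed. If such a patient is analysed as having no DRP, the event rate is understated in both arms and the difference between arms shrinks with it.

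The full protocol or an analysis plan could add call-back rules. As the article fixes the period and the window, however, they do not fit each other, and no later analysis can recover days that had not yet happened when the only call was made.

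**Working it through.** **Inputs.** From Sample size calculation: "We hypothesized a DRP rate of 45% in the experimental group as compared to 60% in the control group" and "Considering a 90% power and a 5% two-sided alpha level, we would need 235 patients per group". From Outcomes and the abstract: a 7-day period with calls on days 5 to 9, and a 35-day period with calls on days 30 to 40. The article gives neither the distribution of call days nor the timing of DRPs within the week, so both are assumed below.

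**Step 1: the plan's own figure.** The usual pooled formula without continuity correction is

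n = [1.960 × √(2 × 0.525 × 0.475) + 1.282 × √(0.60 × 0.40 + 0.45 × 0.55)]² / 0.15² ≈ 231 per group.

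The stated 235 is within 2% of this. At 235 per group the power is 90.5%. I use 235 as the effective size throughout, because the plan's inflation factor deals with clustering separately.

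**Step 2: share of the period observed.** A day-5 call covers 5/7 = 71% of the period, a day-6 call 6/7 = 86%, and a day-30 call 30/35 = 86%.

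**Step 3: risk seen at an early call.** Under a constant hazard, the risk by day t is 1 − (1 − p)^(t/7).

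- Control, p = 0.60: 48.0% by day 5 and 54.4% by day 6, so 12.0 and 5.6 points are missed.
- Experimental, p = 0.45: 34.8% by day 5 and 40.1% by day 6, so 10.2 and 4.9 points are missed.

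**Step 4: calls spread evenly over days 5 to 9, counting events only to day 7.** One fifth of patients are seen to day 5, one fifth to day 6 and three fifths to day 7. For control under a constant hazard this gives (48.0 + 54.4 + 3 × 60.0)/5 = 56.5%. Under linear accrual the multiplier is (5/7 + 6/7 + 3)/5 = 0.914. If 90% of events occur by day 5 (and 95% by day 6), it is (0.90 + 0.95 + 3)/5 = 0.970.

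| Accrual of DRPs (assumed) | Control | Experimental | Difference (points) | Power at 235 per group |
|---|---|---|---|---|
| Full 7 days observed | 60.0% | 45.0% | 15.0 | 90.5% |
| Constant hazard | 56.5% | 42.0% | 14.5 | 88.5% |
| Linear | 54.9% | 41.1% | 13.7 | 84.7% |
| 90% of events by day 5 | 58.2% | 43.7% | 14.5 | 88.6% |
| 95% of events by day 5 | 59.1% | 44.3% | 14.8 | 89.6% |

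**Step 5: outer limit of the window.** If every call were made on day 5, the rates would be 48.0% v 34.8% with 83.4% power (constant hazard), or 42.9% v 32.1% with 67.1% power (linear). Nothing in the article suggests this pattern.

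**Step 6: hospitalization.** The article gives no rate. For an assumed 35-day risk of 5% to 20% and a constant hazard, a day-30 call misses 0.7 to 2.6 points.

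**The case against.** A symmetric contact window is an ordinary feasibility choice, and several points in the plan's favour stand.

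- The primary outcome is any DRP. A patient who already has one by day 5 or 6 is classified correctly, and only patients still free of one are incompletely observed. It would go too far to say that the outcome cannot be measured in patients called early.
- A wrong product, or a drug the pharmacy could not supply, plausibly arises at the first visit after discharge. That would shrink the loss. Not taking what was prescribed, or continuing stopped treatment, can begin later in the week.
- The window is the same in both arms, each unit contributes to both arms, and the Discussion section says two study pharmacists make the assessments centrally to favour uniform interviews.

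A reader might infer two stronger faults.

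The first is that observation runs from 5 to 9 days, so that late calls inflate the rate. The definitions do not support this. They limit the outcomes to the seven and the 35 days, and a day-9 call can ask about days 1 to 7. By the stated definition the observed time is 5 to 7 days.

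The second is that the window creates a spurious treatment effect. With no true effect and 60% in both arms, calling one arm on day 5 and the other on day 7 would produce a false 12.0-point difference; day 6 against day 7 would produce 5.6 points. The first figure needs every patient in one arm called on day 5 and every patient in the other on day 7. Open assessment means differing call days cannot be ruled out, but the article gives no evidence of them.

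None of this removes the remaining mismatch: an event-free patient called early is not followed for the whole period.

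**Conclusion.** The point holds as a modest flaw in how the call windows are set. Early calls leave event-free patients unobserved for up to 2 of 7 days for the primary outcome and up to 5 of 35 days for hospitalization.

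With equal call timing in the two arms, the consequence is attenuation. The difference falls from 15 points to about 14 to 14.5, and power falls from 90.5% to about 85% to 89%, with less loss if DRPs cluster at first dispensing. These figures assume evenly spread calls, the accrual patterns in the table, and early event-free patients analysed as having no DRP. The article specifies none of the three. Bias between arms remains conditional on call day differing by arm. The change is worth making because it costs little and lets the call observe the outcome as defined.

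**What to change.** **Units not yet started.** Open the calls no earlier than the last day of each period, for example days 7 to 9 and days 35 to 40, and ask only about events up to day 7 and day 35. Apply this to both periods of such a unit. A change made between a unit's two periods would coincide with the change of arm and would itself create a difference in call timing. At the time of the article (Trial status) 340 patients had been included. At 14 patients per period and two periods, that equals about 340/28 ≈ 12 units' worth, so much of the recruitment probably still lay ahead.

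**Patients already called.** Report the distribution of call day by arm. Add a sensitivity analysis that excludes patients who were event-free when called before day 7 (or day 35). Because early-called patients with an event stay in, this analysis tends to overstate the rate, whereas counting the excluded patients as event-free understates it. The two should be read together as a bracket.

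**Cost.** The change is to the call schedule and the interview wording. Days 7 to 9 and 35 to 40 add no recall beyond what the plan already allows, but the shorter window may leave a few more patients unreached. Extending the upper end to recover them would lengthen recall slightly.

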### Statistical analysis

The primary analysis will be conducted within the framework of a hierarchical model, inspired by the work of Turner *et al*.
[30]. Under this model, two levels of correlation are considered: intra-cluster correlation and cross-correlation period. Secondary outcomes will also be analyzed with hierarchical models. Subgroup analyzes will consider patient characteristics (age and pathology), drugs classes, nature of the unit (surgery or medical), number of home treatments, day of discharge (weekday or weekend), whether it is an expensive drug (more than 150€ per unit) is prescribed, and whether some medications require temperature control.

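### The severity outcome is defined on identified DRPs, a set the intervention is expected to change, so as written it is not a comparison of the randomised groups

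*Protocol article*

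**What the plan says.** The Outcomes section defines the primary outcome at patient level: "The primary outcome is a composite one comprising of any problem or dysfunction observed during the seven days after discharge". It then describes the grading, which starts from DRPs already found: "For each DRP, an expert committee composed of physicians" (with a clinical pharmacist among the members) "will assess the potential medical impact of the DRP in terms of its severity (from 0: no problem, to 3: life-threatening"). The outcome follows directly: "The severity of the identified DRP will be one of the secondary outcomes".

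The Background puts the aim in the same terms: "The potential harmfulness of DRPs will be appraised by an expert committee". The Statistical analysis section adds only: "Secondary outcomes will also be analyzed with hierarchical models". Nowhere does the article give a version of severity that covers all patients, and no value is assigned to a patient without a DRP.

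The planning assumption in the Sample size calculation section is: "We hypothesized a DRP rate of 45% in the experimental group as compared to 60% in the control group". The Blinding section says that the trial is open and that the committee's grading is the only blinded outcome.

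**The concern.** A severity grade exists only where a DRP has been found. Finding one is the event that the intervention is meant to prevent. If the trial works as planned, the graded sets in the two arms differ in size and probably in composition, and randomisation no longer makes them comparable. A hierarchical model deals with correlation within units and periods; it does not undo this selection.

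The stakes are in interpretation. The primary composite counts any problem, whatever its consequence, so readers will look to severity to judge whether a fall in DRPs matters. They may also give it extra weight because the grading is blinded. A comparison among DRPs could then show no difference, or a worse severity mix, alongside a real reduction in serious DRPs.

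**Working it through.** **The plan's own figure.** Inputs from the Sample size calculation section: 60% versus 45%, two-sided 5%, 90% power, and "Considering a 90% power and a 5% two-sided alpha level, we would need 235 patients per group" under individual randomisation. With pooled variance under the null,

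n = [1.960·√(2 × 0.525 × 0.475) + 1.282·√(0.60 × 0.40 + 0.45 × 0.55)]² / 0.15² ≈ 231 per group.

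The unpooled form gives 228 and the continuity-corrected form 244. The stated 235 is within 3% of 231, so the 60% and 45% rates are confirmed as the planning inputs. The article gives no figure for severity.

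**Size of the graded sets.** On 235 per group, 0.60 × 235 = 141 control patients and 0.45 × 235 ≈ 106 experimental patients would have a DRP to grade.

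**Assumptions for the illustration (not in the documents).** One DRP per affected patient; DRPs split into mild and serious; mild share of control DRPs between 50% and 80%. Let s be the proportion of all control patients with a serious DRP and x the reduction in that proportion. The serious share among DRPs is s/0.60 in control and (s − x)/0.45 in the experimental arm.

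**Case 1: only mild DRPs prevented (x = 0).** The share is multiplied by 0.60/0.45 = 1.33.

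| Mild share of control DRPs | Serious, all patients (both arms) | Serious share among DRPs, control | Serious share among DRPs, experimental |
|---|---|---|---|
| 50% | 30% | 50% | 66.7% |
| 60% | 24% | 40% | 53.3% |
| 70% | 18% | 30% | 40% |
| 80% | 12% | 20% | 26.7% |

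The same happens with mean scores. Take the 60% row, with mild scored 1 and serious 2:
- Among DRPs: control (0.36 × 1 + 0.24 × 2)/0.60 = 1.40; experimental (0.21 × 1 + 0.24 × 2)/0.45 = 1.53, apparently worse.
- Over all patients, with no DRP scored 0 for this arithmetic: 0.84 versus 0.69, better.

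**Case 2: mostly mild DRPs prevented, some serious.** Mild share 60%, with 12 points of mild and 3 points of serious prevented. Serious DRPs over all patients fall from 24% to 21%. The share among DRPs rises from 40% to 0.21/0.45 = 46.7%.

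**Case 3: proportional prevention.** Serious DRPs fall from 24% to 0.24 × 0.75 = 18% of all patients. The share among DRPs is 0.18/0.45 = 40%, unchanged.

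**Case 4: only serious DRPs prevented.** Serious DRPs fall from 24% to 9% of all patients, and the share among DRPs falls from 40% to 0.09/0.45 = 20%. Here both measures point the same way.

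**General rule.** (s − x)/0.45 exceeds s/0.60 whenever x < 0.25·s. So the share among DRPs looks worse whenever serious DRPs fall by less than 25% in relative terms, which is the planned relative fall in all DRPs (0.15/0.60). At exactly 25% it shows nothing.

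**The case against.** The strongest reply is that the article describes what is graded and by whom, not how it is analysed. A committee can grade only DRPs that exist. No denominator, unit of analysis or summary measure is stated for severity, and a worst grade per patient could be built from the same grades. An analysis plan that is not shown may do so. This stands in part: a reader might infer that the article expressly excludes patients without a DRP, and it does not say that. What remains is that the outcome itself is defined on identified DRPs, which goes further than leaving an analysis set open.

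A reader might also infer that preventing mild DRPs is bound to look like harm. That needs both an analysis restricted to DRPs and prevention weighted towards mild ones. The documents give no severity distribution, and Cases 3 and 4 show no apparent harm.

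Nor do the documents make severity the main measure of clinical relevance. Unplanned hospitalisation to day 35 is also a secondary outcome, is the only one named in the Abstract, and does not depend on having a DRP. The Background's sentence on secondary objectives names satisfaction and subgroups, not severity.

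Finally, grade 0 is on the scale for a graded DRP, so scoring patients without a DRP as 0 would merge two different states. That objection is sound and shapes the fix.

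**Conclusion.** The point holds in this form: as worded, the severity outcome compares the arms within a set selected by the primary outcome, so it cannot be read as an effect of the intervention in the randomised groups. That follows from the definition and the planned fall from 60% to 45%.

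The size and direction of any distortion rest on assumptions: one DRP per affected patient and a severity mix that the documents do not supply. Under them, the serious share among DRPs is inflated by up to a factor of 1.33 when no serious DRP is prevented, and is unchanged when serious DRPs fall in proportion.

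The primary conclusion is unaffected. Blinded grading does not remove the selection, because DRPs are detected beforehand by an unblinded pharmacist. It is a change that should be made, not one on which the trial's validity turns.

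**What to change.** Define severity for every enrolled patient, in one or both of these forms, analysed in the planned hierarchical framework:

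- the worst committee grade per patient, as an ordered outcome with no DRP as its own lowest category, below grade 0;
- the proportion of all patients with at least one DRP at or above a grade cut-off fixed in advance.

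Present the distribution of grades among DRPs by arm descriptively, without a test or an effect claim. State in the report that detection of DRPs was open although grading was blinded, since the per-patient measure still depends on open detection.

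The cost is a few lines in the outcome definition and analysis plan, written before severity is analysed by arm. The interviews and committee grades needed are those already planned.

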## Discussion

This study will investigate the effect of HP reconciling medications with the patient at discharge and communicating with the patient’s CP on preventing DRPs. The subgroups study will evaluate the patients for which the process would be efficient. The French Society of Clinical Pharmacy is expected to write recommendations and promote communication between HPs and CPs. We expect a decrease in DRPs from 60 to 45%.

The success of the study depends on the ability of the HP to enroll patients in the study. The units have been chosen for their possibility of having more than one discharge a day. Most are surgery units (orthopedic, urology, or general surgery) and medical units (nephrology, gastroenterology, internal medicine, and so on) with a large number of beds (more than 20) and a mean length of stay from 5 to 11 days. Patients in the intervention group need to spend only a few minutes of discussion with the HP. This intervention will need to be performed as soon as possible once discharge is planned. Indeed, at discharge, patients are usually stressed with transport and other administrative issues, so they may be less receptive to discuss their treatment.

To optimize and standardize the intervention assessed, the scientific committee has established a training program for HPs. Also, quality documents have been written to ensure performance of the same intervention. Outcome assessments will be performed centrally by two pharmacists (pharmacists in charge of the study) specially recruited for the study, which will favor homogeneity in the phone interviews.

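### The subgroup set is not fixed: Outcomes and Statistical analysis list different factors, drug-based membership could depend on arm, and the claims about who benefits go beyond the design

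*Protocol article*

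**What the plan says.** The Background section makes subgroup analyses a secondary objective.

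The Outcomes section states that "DRP will be studied in following five subgroups". The first is age, cut at 75 years. The others are "2/less or over or equal to 4 drugs prescribed 3/expensive or not-expensive medication 4/surgery or medical-unit and 5/planned or non-planned hospitalization".

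The Statistical analysis section gives another list: "Subgroup analyzes will consider patient characteristics (age and pathology), drugs classes, nature of the unit (surgery or medical), number of home treatments", followed by day of discharge (weekday or weekend), prescription of an expensive drug (over 150€ per unit) and medication needing temperature control. That makes eight factors.

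Under Intervention, the hospital pharmacist checks the discharge prescription and, where needed, takes it up with the physician. In the control group there is no reconciliation at discharge. Among the measures in Outcomes is "the proportion of drug prescriptions modified by the HP at discharge".

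On use of the results, the abstract says: "It will allow for identifying the type of patients in France for which the intervention is most relevant". The Discussion says: "The subgroups study will evaluate the patients for which the process would be efficient". The Sample size calculation section addresses only the overall difference, 60% versus 45%.

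**The concern.** Prespecification protects a subgroup analysis only if there is one specified set. Here a reader of the final report could not tell whether the five or the eight factors were planned, or which drug count was meant. The Blinding section describes the trial as fully open, and Trial status reports 340 patients already included, so a choice left open now could be made with knowledge of the data.

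The second issue is validity. Randomization protects a within-subgroup comparison only if membership does not depend on the arm. A factor read from a prescription that the intervention can alter may fail that condition.

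The third is interpretation. The subgroup results are presented as showing which patients should receive the service, and the Discussion expects professional recommendations to follow.

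**Working it through.** **1. The two lists side by side**

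| Factor | Outcomes | Statistical analysis |
|---|---|---|
| Age | yes, cut at 75 | yes, no cut-off |
| Unit type | yes | yes |
| Expensive drug | yes, no threshold | yes, over 150€ per unit |
| Drug count | drugs prescribed, cut at 4 | home treatments, no cut-off |
| Planned or unplanned admission | yes | no |
| Pathology | no | yes |
| Drug classes | no | yes |
| Day of discharge | no | yes |
| Temperature-controlled drug | no | yes |

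Three factors are common, one appears under two definitions, one is only in Outcomes and four are only in Statistical analysis. The union is 3 + 1 + 1 + 4 = 9 factors, or 10 if the two drug counts are separate. Neither list contains the other, and neither has all the cut-offs.

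**2. Can membership depend on arm?**

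The count "less or over or equal to 4 drugs prescribed" is not tied to the home, admission or discharge prescription. Suppose it is the final discharge prescription. A patient leaving with exactly 4 drugs, one of which is stopped after the pharmacist's check, falls in the lower group in the experimental period. The same patient in the control period stays in the upper group. The subgroups then hold different kinds of patients by arm. The same reasoning applies to expensive medication, drug classes and temperature-controlled drugs. It does not apply to age, unit type or planned admission. The documents give no rate of prescription changes, so the size of this bias cannot be calculated.

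**3. What the trial can say about interactions**

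Inputs from Sample size calculation: 60% versus 45%, 90% power, two-sided 5%, 235 per group, ρ = 0.2, η = 0.1, inflation factor 1 + (P − 1)ρ − Pη.

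Reproducing the plan's figure with the pooled normal formula: n = [1.96·√(2 × 0.525 × 0.475) + 1.2816·√(0.24 + 0.2475)]² / 0.15² = 231 per group, within 2% of 235.

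Size scenarios: the section names 46 units, but its total of 1,176 equals 14 × 2 × 42, whereas 14 × 2 × 46 = 1,288. I therefore use a range.

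- Low end, 42 units × 10.2: inflation 1 + 9.2 × 0.2 − 10.2 × 0.1 = 1.82; effective size per arm 428.4 / 1.82 = 235.
- High end, 46 units × 14: inflation 1 + 13 × 0.2 − 14 × 0.1 = 2.2; effective size per arm 644 / 2.2 = 293.

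Assumed interaction (none is given): 22.5 points in one half and 7.5 in the other, control rate 60% in both. The difference is 15 points, as large as the whole planned effect. The four binomial variances sum to 0.24 + 0.2344 + 0.24 + 0.2494 = 0.96375. Then SE = √(0.96375 / half the effective size per arm), and power = Φ(0.15/SE − 1.96).

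*Unit-level factor.* Each pharmacist selected one surgical and one medical unit, so the split is about 50/50 and the full inflation applies within each half.

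- Low end: SE = √(0.96375/117.7) = 0.0905; power 38%.
- High end: SE = √(0.96375/146.4) = 0.0811; power 46%.
- Smallest interaction detectable with 80% power: 2.80 × SE = 23 to 25 points.

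*Patient-level factor, favourable case.* Both levels occur in the same unit-period, so shared effects largely cancel. I take a design effect of 1 − ρ = 0.8 and no variation of the interaction between units.

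- Low end, 50/50: SE = √(0.96375/267.75) = 0.0600; power 71%.
- High end, 50/50: SE = √(0.96375/402.5) = 0.0489; power 87%.
- A 20/80 split gives 52% and 69%.

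A very large interaction (30 versus 0 points) in a 50/50 split has power above 90% even for a unit-level factor.

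**The case against.** The strongest reply is that only the mismatch between the lists is certain.

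- A reader might infer that a subgroup is in fact defined on the altered prescription. The documents do not say so. Outcomes leaves the counting point open, and the home-treatment wording in Statistical analysis can be read as a count before the intervention. The hazard is conditional and should be stated that way.
- A reader might infer that the trial cannot support any finding on who benefits, or apply the low power for unit type to every subgroup. That carries the full cluster inflation to factors that vary within a unit-period, which most of the listed factors do. Section 3 of the working shows materially higher power there under favourable assumptions.
- A reader might compute a chance of 1 − 0.95⁹ = 37% of at least one false-positive interaction. That needs nine independent tests, each at an unadjusted 5%, and the article states no such plan. Interaction tests and multiplicity rules may properly stand in an analysis plan that is not shown, so their absence is not held against it.
- Nothing shows that the Outcomes list should prevail. It also lacks the 150€ threshold.
- The statements on who benefits are narrative and set no decision rule, and the primary analysis is untouched.

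All of this stands as a limit on the point. It does not remove the contradiction: the article prints both lists, one with a stated number, so condensation does not explain the difference.

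**Conclusion.** The point holds in three parts of unequal certainty.

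- Certain: the two sections give incompatible sets, five against eight factors, with different drug-count definitions, for a declared secondary objective in an open trial.
- Conditional: if drug-based factors are read from the final discharge prescription, membership can depend on arm. The size is unknown.
- A matter of degree: the trial is sized only for the overall effect. For unit type, power for an interaction as large as the planned effect is about 38–46%. For balanced patient-level factors it may reach 71–87%, and less with unequal splits. These figures rest on assumed interaction sizes and subgroup shares, the protocol's own correlations and a normal approximation. The subgroup results are best regarded as exploratory, and the certainty in the abstract and the Discussion is not justified.

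The matter should be corrected. It does not threaten the primary analysis.

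**What to change.** 1. State one reconciled list, chosen by the authors, identically in Outcomes and Statistical analysis, before any outcome is compared by arm.
2. Give each factor one definition and cut-off in both places, including the 150€ threshold now found only in Statistical analysis and the age and drug-count cuts now found only in Outcomes.
3. Define every drug-based factor (count, cost, class, temperature control) on the home treatment list, or on the prescription as it stood before hospital pharmacist review, recorded the same way in both periods.
4. Label any factor outside the agreed list exploratory.
5. Reword the abstract and the Discussion so that the trial explores, rather than identifies, which patients benefit most.

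Cost: wording, recording the pre-review prescription status, and a more modest claim. No change to sample size or primary analysis.
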